### Outcome measurements

A computer-based, self-reported patient questionnaire is used to collect data on back pain-related functional limitation, pain intensity, general health, HRQoL, and working status. Back pain-related functional limitation is measured by using the Oswestry Disability Index (ODI), pain intensity by using the Numeric Rating Scale (NRS), general health by using the general self-rated health (SRH) question and HRQoL is measured by the EuroQol 5 Dimensions 3 Levels (EQ-5D-3L) instrument [30–33].

#### Primary outcome measure

##### Oswestry Disability Index (ODI) − A measure of back pain-related functional limitation

The ODI is a condition-specific instrument that measures back pain-related functional limitation [30]. It consists of ten questions where each question has six response choices and the value of each question ranges from 0 (no problems) to 5 (worst imaginable problems). A total ODI score is computed as the sum of scores on each question, and the total score of ODI varies between 0 (no problems) and 50 (worst imaginable problems). The total ODI score is then normalised to 0–100, by multiplying the (unadjusted) total score by 2. The ODI normalised score, based on the ODI outcome measure at 6 months, is our primary outcome measure [12]. The ODI has a high reliability, validity, and responsiveness, and is easy to administrate and is sensible to find clinical changes in treatment of patients with CLBP [34, 35].

#### Secondary outcome measures

##### Numeric Rating Scale (NRS) – A measure of pain intensity

The NRS is an 11-grade scale ranging from 0 (no pain) to 10 (worst pain imaginable). The NRS is often used in clinical trials and by clinicians to measure self-reported pain intensity. It is easy to administrate and has a high responsiveness [31]. Each participant is asked to state their currently experienced pain using the NRS.

##### Self-rated health (SRH) – A measure of general health

As a measure of general health, a self-rated health (SRH) question will be used. The SRH question is phrased as: ‘In your opinion, what is your health status? Is it very good, good, fair, bad, or very bad?’ We use a pre-scored Swedish experienced-based value set (as presented in the Online Resource with supplementary material to Burström et al. 2014 [32]), to transform SRH severity levels into quality-of-life (time-trade off) values.

##### EQ-5D-3L – A measure of health-related quality of life

The EQ-5D-3L is a generic instrument measuring HRQoL. The EQ-5D-3L is a questionnaire consisting of five dimensions with three severity levels and a Visual Analogue Scale (VAS) ranging from 100 (best imaginable health state) to 0 (worst imaginable health state) [33]. The dimensions and levels result in 243 possible EQ-5D health states. Each health state can be assigned a value based on country-specific value sets. We use the Swedish experienced-based value set to transform EQ-5D health states into HRQoL (time-trade off) values [32]. The EQ-5D-3L is a valid instrument among patients with pain [31, 36]. The EQ-5D-3L is commonly used in Swedish health care and enables cross-sectional comparisons.

##### A measure of working status

The study participants will be asked to answer questions about current working status and number of hours absent from work due to illness during the past 7 days. For each participant, working status is defined as self-reported percentage of full-time work.

#### Exploratory outcome measures

##### Costs and quality-adjusted life years (QALYs)

We will analyse the difference in costs during 12 months after the randomisation between the different treatment groups. Both direct and indirect costs will be estimated. Direct costs include costs for pharmaceuticals, health care visits, clinical examinations, and hospital days. Information about each participant’s resource consumption is collected by using a computer-based questionnaire. At each follow-up occasion (at baseline, and at 3, 6, and 12 months after baseline) the participant is asked to recall their resource consumption during the last 3 months (quantities of resource consumption is, e.g. number of prescriptions, number of visits to health care providers, number of clinical examinations, and number of hospital days). To estimate the direct costs the quantities of resource consumption is multiplied by the unit costs. Unit costs of pharmaceuticals are collected from the price database available at TLV and unit costs for health care visits will be based on prices in the Stockholm County Council for primary health care [37, 38]. Unit costs for clinical examinations and hospital days will be based on unit costs in the Stockholm County Council and in the southern part of Sweden (Region Skåne) [39].

The indirect costs refer to costs of changes in productivity (labour production) [40]. Data on changes in productivity while being at work (presenteeism) is not collected in the study. The working status of each participant, defined as the percentage of full-time work, was recorded at baseline and at 3, 6, and 12 months after baseline. The working status is estimated as the percentage of full-time work for each participant. The labour production value was estimated for the period from the first visit (at baseline) until 3 months, and for 4 to 6 months, and for 7 to 12 months. The average working status during the first of these periods (0–3 months) was assumed to be an average of the working status at baseline and 3 months. The average working status during the other periods (4–6 months and 7–12 months) was calculated equivalently. To estimate the value of production for the first 12 months the average working status during the first 12 months will be multiplied by the average value of labour production of a Swedish worker [40, 41].

To estimate the number of QALYs for each treatment the quality-of-life values based on EQ-5D-3L will be used. The average number of QALYs during 12 months is calculated as the area under the curve during 12 months. A treatment is defined as cost-effective if the treatment is less costly while providing the same or better health outcomes, or if the added cost of the treatment is reasonable in comparison to the health outcomes obtained, in which case the incremental cost per gained QALY is estimated. An intervention is in the latter case defined as cost-effective if the cost per QALY gained is below or equal to a threshold value corresponding to how much society is willing to pay in order to gain a QALY. Different threshold values for a QALY have been used in cost-effectiveness studies and the value has usually been set to around US$50,000 (corresponding to approximately SEK 400,000 using the average exchange rate during 2016 of 1 US$ = SEK 8.6). However, Neumann et al. (2014) argue for using a threshold value of either US$100,000 or 150,000 for a QALY and that a threshold value of US$50,000 should be interpreted as a lower boundary [42]. If the threshold value of a QALY is derived from the literature on the value of a statistical life, even higher threshold values are derived (US$100,000–400,000) [42, 43]. In Sweden, the Swedish Transport Administration (STA) uses a value of a statistical life of SEK 24 million in cost-benefit analysis of road investments. Using this figure, a value per QALY gained of about SEK 950,000 can be derived (US$110,000). In our study, we define an intervention to be cost-effective if the cost per gained QALY is equal to or below SEK 900,000 (US$100,000).

The cost-effectiveness analysis will be reported in accordance with the Consolidated Health Economic Evaluation Reporting Standards (CHEERS) [44] and good research practices on how to conduct cost-effectiveness analysis alongside clinical trials [21]. Unit costs, data sources, and mean use of health care resources will be reported for each treatment. Mean costs for each treatment will be presented as well as incremental costs and effectiveness.

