With limited health care resources and stretched health care budgets, it is important to strive for efficient use of scarce resources [17]. Economic evaluation is a method for assessing costs and effectiveness of alternative ways of allocating resources to assist decisions aimed at improving efficiency [17, 18]. It also constitutes an important input for guiding clinical decisions. To be useful for decision-makers as an input to improve decision-making on the societal efficiency of the allocation of health care resources, it is important that the economic evaluation is based on a societal perspective, including costs both within (e.g. costs for pharmaceuticals, and costs for hospital and ambulatory care) and outside (e.g. indirect costs for decreased labour production) the health care system [18, 19]. In economic evaluations it is common to carry out cost-effectiveness analyses, where costs are measured in monetary terms and effectiveness in non-monetary terms. In this type of analysis, where the aim is to maximise the health gains for a specific cost constraint, it is crucial to use an outcome measure that combines effects on quality and quantity of life into one measure. The most commonly used measure of this sort is the quality-adjusted life year (QALY) [17]. This type of outcome measure is also recommended by, e.g. the National Institute for Health and Care Excellence (NICE) in England and Wales, and by the Dental and Pharmaceutical Benefits Agency in Sweden [20, 21].

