### Data collection

Data will be collected at baseline (after randomisation and before the treatment starts), and at follow-up, 3, 6, and 12 months after baseline. Each participant fills out a computer-based questionnaire at each measurement occasion. The day before each follow-up occasion, each participant is sent a reminder by email to fill out the questionnaire. If needed, a second and a third reminder is sent 2 and 7 days after the follow-up occasion. All data will be obtained from the computer-based questionnaire and from the chiropractor and/or physiotherapist reporting the number and content of treatments.

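### Neither production-loss measure is built to capture work time spent attending treatment, which probably understates, modestly, the incremental cost of the three active arms

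*Protocol article*

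**What the plan says.** The aim covers medical costs and costs for production losses. The Background adds that, for decision-making, "it is important that the economic evaluation is based on a societal perspective", including costs outside the health care system.

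Under Costs and quality-adjusted life years (QALYs), the cost items are as follows.

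- **Direct costs:** "Direct costs include costs for pharmaceuticals, health care visits, clinical examinations, and hospital days". "To estimate the direct costs the quantities of resource consumption is multiplied by the unit costs". Visits are therefore counted and priced.
- **Indirect costs, base case:** labour production, valued from working status at baseline and at 3, 6 and 12 months. A measure of working status says: "For each participant, working status is defined as self-reported percentage of full-time work". Between occasions the end points are averaged. For the first three months the value "was assumed to be an average of the working status at baseline and 3 months", and the later periods follow the same rule.
- **Indirect costs, sensitivity analysis** (Statistical analysis, Exploratory outcome measures): based on the questionnaire item on "number of hours absent from work due to illness during the past 7 days", averaged in the same way and multiplied by an hourly value of labour production.

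Presenteeism is said not to be collected. Time spent attending treatment is not mentioned there, nor among the limitations in the Discussion.

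Under Study treatments, the advice arm receives oral and written information. The other three arms add physiotherapy, chiropractic care or both, with the number of sessions left to the clinicians. Data collection states that data also come "from the chiropractor and/or physiotherapist reporting the number and content of treatments".

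**The concern.** A treatment visit has two costs from a societal viewpoint: the price of the session, and the work lost by a patient who attends in working hours. The plan counts the first and has no measure designed for the second. The arms differ by design in whether a course of treatment is given, so the omission is unlikely to cancel between arms. It would lower the incremental cost of the active arms against advice.

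The incremental cost per QALY, the cost-effectiveness acceptability curves and the SEK 900,000 decision rule would then lean slightly towards the active arms. The protocol also calls a treatment cost-effective if it costs less with the same or better outcomes. If outcomes are similar, the sign of a small cost difference decides the matter.

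**Working it through.** The protocol states no figure on this point, so there is none to reproduce. The check has two parts.

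**1. Could either measure register attendance time?**

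*Base case.* Take 4 to 12 extra visits, 1 to 2 work hours per visit, 50 to 100% of visits in working time and a work year of 1,800 hours. All of these are assumptions. Share of full-time work = visits × hours × working-time share ÷ 1,800.

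- Low: 4 × 1 × 0.5 ÷ 1,800 = 0.11%
- High: 12 × 2 × 1.0 ÷ 1,800 = 1.33%

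A self-reported percentage of full-time work is unlikely to move by so little.

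*Sensitivity analysis.* There are two obstacles.

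- The item asks for absence caused by illness, which does not clearly include leaving work for an appointment.
- The windows are single weeks. Baseline is collected before treatment starts. The other three windows cover 3 × 7 = 21 days of the year and are averaged across the periods between them. If treatment is concentrated in the weeks after baseline (an assumption), most visits fall between the baseline and 3-month windows and are represented by neither.

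**2. How large could the omission be?**

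Omitted cost = extra visits × work hours per visit × value per hour × share in working time. QALY equivalent = omitted cost ÷ threshold. The SEK 900,000 threshold is the protocol's decision rule. SEK 400,000 is its approximate conversion of US$50,000 and lies within the planned curve range of SEK 0 to 1,500,000. The other inputs are assumed.

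| Case | Visits | Hours | SEK/hour | Share | Cost (SEK) | QALY at 900,000 | QALY at 400,000 |
|---|---|---|---|---|---|---|---|
| Low | 4 | 1 | 250 | 0.5 | 500 | 0.0006 | 0.0013 |
| Middle | 8 | 1.5 | 300 | 1.0 | 3,600 | 0.0040 | 0.0090 |
| High | 12 | 2 | 400 | 1.0 | 9,600 | 0.0107 | 0.0240 |

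These values are for a full-time worker. They fall in proportion for part-time workers and are zero for those not working.

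In net-benefit terms, the planned calculation is 900,000 × incremental QALYs − incremental cost. Adding the missing item lowers this by SEK 500 to 9,600. A decision would change only if the planned net benefit were positive and smaller than the omitted amount, that is, within about 0.0006 to 0.011 QALY of the threshold.

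**The case against.** The strongest reply is that the main visit-driven cost is already counted. A reader might infer that attendance time is the only cost that rises with visits. The document does not support that, because visits are a listed direct cost multiplied by a unit price. What is left out is the production loss that goes with the visit.

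Other replies also carry weight.

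- **Size and ordering of the bias.** One might infer an omission near zero in the advice arm, larger with one treatment and largest with two. The document does not establish this. Session numbers are discretionary, and Recruitment procedures neither permits nor prohibits concomitant care, so advice-arm patients may also lose work time to treatment elsewhere. More attendance in the active arms is the natural expectation from the design, but no visit difference can be read from the text.
- **Scope.** One might read the societal perspective as requiring travel costs. That sentence is general Background, and the aim is limited to medical costs and production losses. Travel expense lies outside that scope, and leaving it out is no contradiction. Lost work time is within it.
- **Existing sensitivity analysis.** Varying unit costs by ±50% also varies visit prices, and a time cost per visit acts like a higher price. Whether +50% covers the missing amount depends on a visit price the protocol does not give, and the base case is unaffected either way.
- **Partial capture.** Some visits fall outside working hours, and some attendance may be reported as illness absence. This reduces the size without removing the likely direction.
- **Condensed article.** A full costing inventory may be held elsewhere. The article does, however, state the production measures, the averaging rule and the valuation, and the point rests on those.
- **Status.** Costs and QALYs are exploratory outcomes, and the primary outcome is untouched.

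**Conclusion.** The point holds in a limited form. Visits are costed at clinic price, but neither the percentage of full-time work nor the 7-day illness-absence item is built to capture work time lost in attending treatment. Given the design, this probably understates the active arms' incremental production loss against advice.

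The likely effect is modest: SEK 500 to 9,600 per patient, or 0.0006 to 0.011 QALY at SEK 900,000. That range rests wholly on assumed visits, hours, hourly value and working-time share. It could matter if the QALY gain is about 0.01 or less, if the result lies near the threshold, or if costs and outcomes are almost equal. No reversed decision is demonstrated, and a strict ranking of the bias across the three active arms is not established.

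**What to change.** Add one pre-specified sensitivity analysis to Statistical analysis, Exploratory outcome measures. In all four arms, add to indirect costs:

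number of visits × assumed work time lost per visit × share of visits in working time × the hourly production value already planned × the participant's percentage of full-time work.

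Specify the following.

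- **Ranges:** for example 1 to 2 hours per visit, and 50 to 100% of visits in working time.
- **Visit counts:** trial treatments from the provider reports and other visits from the questionnaire, with a rule against counting a visit twice. Provider reports alone would miss care obtained elsewhere and could tilt the comparison against the active arms. The 12-month questionnaire recalls only three months, so use the same rule for months 7 to 9 as in the direct-cost calculation.
- **Placement:** add the item to the analysis based on percentage of full-time work. Do not add it on top of the 7-day absence analysis, where attendance reported as absence would be counted twice.
- **Limitation:** state that the base case omits attendance time, and in which direction this probably acts.

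The cost is a few lines of text and no new data collection. The downside is two assumed inputs, time per visit and working-time share, which is why this is better as a scenario than forced into the base case. The active arms may look slightly less favourable.

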#### Baseline

Baseline data will be collected during the first visit or at 1–4 days before the first visit at the PCRU. Data on individual characteristics (age, sex, education, smoking status, physical activity, use of pain killers, and pain duration), outcome measures (back pain-related functional limitation, pain intensity, general health, HRQoL, working status) and resource consumption (pharmaceuticals, health care visits, clinical examinations, and hospital days) are collected.

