#### Additional analysis for percentage point change in ODI

Two additional analyses will be carried out for the primary outcome variable ODI at 6 months. First, an adjusted analysis will be used to control for baseline variables (age, sex, education, smoking status, physical activity, use of pain killers). This multiple linear regression analysis will adjust for potential predictor variables which might reasonably be expected to be predictive of favourable outcomes. We will perform residual analysis to assess model assumptions and goodness-of-fit. Secondly, a subgroup analysis will be performed to detect differences between groups of patients with an ODI normalised score at baseline either less than 40% or equal to or greater than 40% [12].

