#### Exploratory outcome measures

Uncertainty will be reported by estimating 95% confidence intervals for the mean value of costs and effectiveness in each group, and for the difference in mean value of costs and effectiveness between groups. Non-parametric bootstrap analysis will be carried out to estimate the sampling distribution of the ICER estimator in the cost-effectiveness plane (where each treatment is compared with information and advice) [51]. To reflect uncertainty in the threshold value for a QALY, cost-effectiveness acceptability curves will be computed, where the probability of cost-effectiveness is presented for different threshold values (from SEK 0 to 1,500,000). Cost-effectiveness acceptability curves will be computed based on parametric and non-parametric bootstrap methods using the net benefit approach [51]. Sensitivity analysis will also be carried out where the unit costs will be changed (±50%), and where QALYs, instead of being based on EQ-5D-3L, will be estimated based on SRH. In another sensitivity analysis, the indirect costs will be estimated based on number of hours absent from work during the past 7 days. The average number of hours absent from work during the first 3 months was assumed to be an average of the hours absent from work at baseline and at 3 months, whereas the average number hours absent from work during the other periods (4–6 months and 7–12 months) was calculated equivalently. To estimate the loss in production due to absence from work for the first 12 months, the average number of hours absent from work during each period will be multiplied by the average per hour value of labour production for a Swedish worker.

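### The QALY comparison names no adjustment for baseline EQ-5D-3L utility, so it gives up precision and carries part of any chance baseline gap into the cost-effectiveness result

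*Protocol article*

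**What the plan says.** Under Costs and quality-adjusted life years (QALYs), the protocol article says that for QALYs "the quality-of-life values based on EQ-5D-3L will be used" and that "The average number of QALYs during 12 months is calculated as the area under the curve during 12 months". The curve starts at baseline. The Data collection section says "Data will be collected at baseline (after randomisation and before the treatment starts), and at follow-up, 3, 6, and 12 months after baseline", and the Baseline section lists among the measures taken then "outcome measures (back pain-related functional limitation, pain intensity, general health, HRQoL, working status".

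In the statistical section on exploratory outcome measures, 95% confidence intervals are promised for each group's mean and "for the difference in mean value of costs and effectiveness between groups". For the ICER, "Non-parametric bootstrap analysis will be carried out to estimate the sampling distribution of the ICER estimator", and acceptability curves follow by net benefit. The sensitivity analyses listed there vary unit costs by 50% either way, replace EQ-5D-3L by self-rated health (SRH), and value production from hours absent. None brings in baseline utility.

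Production value is built in the same manner: "The average working status during the first of these periods (0–3 months) was assumed to be an average of the working status at baseline and" (the sentence goes on to name the 3-month value), with the later periods handled alike.

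The one covariate list in the document belongs to the additional analysis of the Oswestry Disability Index (ODI) at 6 months: "age, sex, education, smoking status, physical activity, use of pain killers". It contains no utility value. The linear mixed models are described for primary and secondary outcomes; QALYs and costs are classed as exploratory.

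**The concern.** The baseline EQ-5D-3L value cannot be affected by treatment, yet it is part of the area being compared. The later values that make up the rest of the area are likely to correlate with it. If arms differ at baseline by chance, some of that difference appears in incremental QALYs and is then multiplied by the threshold in the net-benefit analysis. For the ODI the authors deal with baseline explicitly, through change scores and an adjusted model. For QALYs the described contrast is a plain difference in means.

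What is at stake is the second research question and the planned cost-effectiveness paper. The Background concedes that power for cost-effectiveness may be low because the sample size is set on clinical endpoints. A free gain in precision is therefore worth having.

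**Working it through.** The plan gives no figure for the QALY comparison, so there is none to reproduce.

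**Inputs from the document:** measurements at 0, 3, 6 and 12 months; threshold SEK 900,000 per QALY; 150 per group with 20% dropout, hence 150 × 0.8 = 120 evaluable.

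**Assumptions (not in the document):** equal utility SD at all times; a common correlation ρ between any two time points, taken as 0.3 to 0.5, with 0 as the floor; utility SD 0.1 to 0.3; an illustrative baseline gap of 0.03; straight-line interpolation. The last is implied for QALYs by the area-under-the-curve wording, and the same averaging is spelled out for working status.

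**1. Weights.** With intervals of 0.25, 0.25 and 0.5 year:
- baseline 0.25/2 = 0.125
- 3 months (0.25 + 0.25)/2 = 0.25
- 6 months (0.25 + 0.5)/2 = 0.375
- 12 months 0.5/2 = 0.25

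They sum to 1. Baseline working status also has weight 1/8 when the three periods are weighted by their length.

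**2. Share of a baseline gap carried through.** Slope of the area on baseline = 0.125 + 0.875ρ.
- ρ = 0: 0.125
- ρ = 0.3: 0.3875
- ρ = 0.5: 0.5625

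**3. Variance removed by adjustment.** The sum of squared weights is 0.28125, so the variance of the area, in units of the utility variance, is 0.28125 + 0.71875ρ. R² = slope²/variance, and the SE is multiplied by √(1 − R²).

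| ρ | variance of area | R² | SE factor | SE reduction |
|---|---|---|---|---|
| 0 | 0.281 | 0.056 | 0.972 | about 3% |
| 0.3 | 0.497 | 0.302 | 0.835 | about 16% |
| 0.5 | 0.641 | 0.494 | 0.711 | about 29% |

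**4. Illustrative gap of 0.03.**
- Mechanical part: 0.125 × 0.03 = 0.004 QALY.
- Total at ρ = 0.3: 0.3875 × 0.03 = 0.0116 QALY; × 900,000 = SEK 10,463.
- Total at ρ = 0.5: 0.5625 × 0.03 = 0.0169 QALY; × 900,000 = SEK 15,188.

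**5. How unusual is 0.03?** One SE of the baseline difference is SD × √(2/120): 0.013, 0.026 and 0.039 for SD 0.1, 0.2 and 0.3. A gap of 0.03 is therefore about 2.3, 1.2 or 0.8 SEs.

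**6. Check by simulation.** With 10,000 trials, 120 per arm, SD 0.2 and ρ = 0.5, the SE of the QALY difference was 0.0206 unadjusted and 0.0147 adjusted (formula: 0.0207 and 0.0147). The slope of the estimate on the baseline gap fell from 0.56 to 0.00. Both estimators averaged zero under no effect, so neither is biased over repeated randomisation.

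**The case against.** The strongest reply is that the document never calls the comparison unadjusted. The area under the curve is a correct definition of a QALY and the remedy keeps it. A covariate-adjusted mean difference with a bootstrap would also fit the wording, and an analysis plan that is not shown could specify one. The article further commits to published reporting standards and good practice for trial-based economic evaluation, whose content cannot be checked here. What stands is that non-adjustment is read from the method described. But the article sets out the estimator, the contrast, the uncertainty method and the sensitivity analyses for this outcome, and none involves baseline utility, although baseline is handled openly for the ODI. Nothing in it shows that the contrast is adjusted.

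Second, participants are individually randomised, so the planned difference is valid on average, and its confidence interval and bootstrap already reflect chance imbalance. That stands in full. The point is about efficiency and conditional bias.

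Third, the sizes depend on correlations, SDs and a gap that the document does not give. That also stands, which is why ranges are shown.

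Fourth, the covariate may not be clean. Baseline data are taken after randomisation, possibly at the first visit, which is also where the participant learns the allocation. This stands and is addressed in the fix.

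**Conclusion.** The point holds as a worthwhile improvement to a valid exploratory analysis. Under equal SDs and a common correlation of 0.3 to 0.5, an unadjusted QALY difference carries 39% to 56% of a chance baseline gap and has a standard error that adjustment would lower by about 16% to 29%. With zero correlation only the mechanical eighth remains and the gain is about 3%.

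The documents do not support three stronger readings that a reader might infer:
- That a baseline gap is counted in full as treatment effect. Only 1/8 enters mechanically; the rest of the carry-over comes through correlation and stays below the whole gap at the correlations assumed.
- That the planned comparison is biased or invalid. Randomisation keeps it unbiased on average.
- That direct costs share the defect. The 1/8 argument covers QALYs and production value only, and no flaw has been shown for direct costs.

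Whether adjustment would change the size or sign of the ICER cannot be said, because the document gives no expected QALY difference.

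**What to change.** - Estimate incremental QALYs by regressing the 12-month area on treatment arm and baseline EQ-5D-3L value.
- Estimate incremental production value by regressing it on arm and baseline working status.
- Fit both regressions within every bootstrap replicate and use them in the net-benefit analysis, so that the correlation between costs and QALYs is kept.
- In the SRH sensitivity analysis, use the baseline SRH value as the covariate in the same way.
- Keep the unadjusted difference as a sensitivity analysis.
- Have the baseline questionnaire completed before the allocation is revealed to the participant.
- Adjusting direct costs for baseline resource use is optional.

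The analysis changes need only wording, since all the covariates are already collected. The questionnaire timing needs an instruction to the units. Because recruitment began on 1 April 2017, it can help only participants not yet seen.
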